**Methods:**

In this proposed cluster randomized study, 9 NHs will be randomly assigned to one of three repositioning intervals (2, 3, or 4 h) for a 4-week period. Each enrolled site will use a single NH-wide repositioning interval as the standard of care for residents at low, moderate, and high risk of PrU development (*N* = 951) meeting the following criteria: minimum 3-day stay, without PrUs, no adhesive allergy, and using VE support surfaces (mattresses). An FDA-cleared patient monitoring system that records position/movement of these residents via individual wireless sensors will be used to visually cue staff when residents need repositioning and document compliance with repositioning protocols.

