## Methods

The TEAM-UP study is a cluster randomized clinical trial with facility-level use of an assigned repositioning interval as the primary intervention and will be conducted at 9 NHs that are all using VE support surfaces. Each participating NH will be randomly assigned to one of three intervention arms. Each arm will have 3 NHs with each NH using a single, NH-wide repositioning interval at either 2, 3, or 4 h as standard of care during the 4-week intervention period. Randomization will occur at the facility level. The sequence in which the repositioning intervals are to be implemented will be randomly ordered and, then assigned to NHs inclusive of each arm of NHs. Thus, 3 clusters of 3 NHs are created with randomly sequenced repositioning intervals.

A secondary cluster is created within each NH as the NH implements its standard risk assessment protocol; residents will be clinically categorized forming clusters by level of risk for developing a new PrU. Level of risk categorization into 3 groups is defined by a Braden score of low (15–18), moderate (13–14), or high (10–12) [32]. All eligible residents will wear a wireless triaxial accelerometer sensor throughout the intervention as part of the NH’s standard of care. Residents may refuse the sensor and can decline to move when prompted by staff as part of their right to refuse care (see Fig. 1). This pragmatic approach offers a unique opportunity to study a single NH-wide repositioning schedule, thus avoiding the potential for staff confusion associated with resident-level random assignment to repositioning intervals, which would require staff to simultaneously execute multiple turning schedules.

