Because we will be examining PrU development from assessment to assessment, the rate of PrU incidence will be modeled as a binary outcome using repeated measures logistic regression and a specified working correlation matrix that models the correlation of responses within subjects. Full likelihood estimation methods are not appropriate for repeated measures logistic regression, so generalized estimating equations (GEEs) will be used instead with model fit assessed using the quasi-likelihood information criterion (QIC). Robust standard errors, clustered at the facility level, will be employed to account for covariance among residents within facilities over time. To test the robustness of models, we will also use non-linear mixed models using PROC GLIMMIX as another option for modeling the data (instead of GEEs using PROC GENMOD). With PROC GLIMMIX, we can use random effects to model the covariance rather than clustered standard errors. As predictors, we will include time-invariant resident characteristics, e.g., age, gender, Medicaid payer, and repositioning schedule, as well as time-varying characteristics, such as resident severity measure, risk level as determined by Braden Scale© score, staffing characteristics (e.g., number, mix, and turnover), and suggested MDS resident data elements as covariates. We may lag some time-varying resident characteristics by one assessment because we want to study the associations of repositioning time with PrU development, controlling for the starting point of the resident for that assessment interval. Interaction variables will be included in the predictor data set.

Residents without PrUs who drop out of the study after at least a three-day stay but before the conclusion of 4 weeks will be included in the analysis based on intent to treat. Residents who develop a Stage 3 or worse PrU, or deep purple discoloration, will be removed from the study per repositioning protocol, but will be considered a completed case if the ulcer developed on the coccyx, sacrum, trochanter or heel. Residents who develop ulcers on sites not thought to be influenced by bed position or limited mobility, or related to sitting, will continue to be followed for analysis, but will not be included in the NH-wide protocol.

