##### Statistical power.

According to previous research, the average PrU incidence rates range from 5.2–15%. At the time of study design, the nine NHs within the NHS were identified with the highest PrU incidence rates which averaged 9.2% (SD = 3.3%). In power analyses, we used 3.5% for PrU incidence as the expected rate for intervention since it is the highest rate found in the TURN study (for moderate-risk patients). The PrU incidence rates have been translated into an odds ratio of 0.38 (= 3.5%/9.2%) as the effect size to detect. For Aim 1, odds ratios from a logistic regression of PrU incidence rates in the three treatment arms (i.e., at 2-, 3-, and 4-h repositioning frequencies), controlling for risk level, are proposed to test the difference in PrU incidence rates between the 4-h arm and the 2-h arm as well as between the 4-h arm and the 3-h arm at 4 weeks; we are assuming that the distance between the 2-h arm and the TURN 3-h odds ratio will be larger. A sample size of *N* = 951 (*n* = 317 for each arm) will be required to detect an odds ratio of .38 with a power of 0.95 at a one-tailed significance level of α = 0.05, according to G*Power. We are using a power of 0.95 instead of the conventional power of 0.80 to ensure that we will have a smaller Type II error to test the hypothesis of no-group difference that we expect to fail to reject. We are using a one-tailed test since we are only interested in determining whether the PrU rate is higher for assigned repositioning intervals longer than the current 2-h standard practice.. For Aim 2, GEE is proposed. A sample size of *n* = 114 for each group (total *N* = 342) will be required to detect an effect size of 5.7% (= 9.2% - 3.5%) with a power of 0.80 at a one-tailed significance level of α = 0.05, using the algorithms GEESIZE developed by Dahmen, et al., on an autoregressive structure for residual correlations [48]. Since the nine NHs will be randomly assigned to the three treatment arms, risk level will be the only potential covariate to be controlled in the models, and this is already considered in the power analyses. Therefore, we will target a sample size of *N* = 951 (the larger of the two required sample sizes) for both aims while taking into account potential losses due to turnover, attrition, and exclusion criteria. While this proposed study may look like a non-inferiority or equivalence trial, we will run regular one-tailed superiority tests, because (as noted earlier) we are only interested in examining whether or not the PrU rate is higher for less frequent repositioning than for the standard 2-h repositioning. (We assume that 2-h repositioning was followed to produce the 9.2% average PrU incidence rate across our 9 study NHs, because that is the current standard of care). Also, according to Snapinn [49], non-inferiority trials have many controversial assumptions and limitations that need to be made or addressed, and that is beyond the control of our study. For incidence, it is difficult to specify a non-inferiority margin for PrU rates. Instead, we will test the hypothesis of no group-difference by examining whether the 95% confidence intervals of the odds ratios (for Aim 1) or the PrU rates (for Aim 2) of the two pairs of compared groups (e.g., 4-h arm vs. 2-h arm and 4-h arm vs. 3-h arm) overlap. If the confidence intervals do overlap, the hypothesis for no-group difference will be confirmed.

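### Facility-clustered robust standard errors with only three homes per arm, as written without a small-sample correction, reject too often and give intervals that are too narrow for the arm contrast

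*Protocol article*

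**What the plan says.** Protocol article, Methods: "Each arm will have 3 NHs with each NH using a single, NH-wide repositioning interval at either 2, 3, or 4 h". The treatment factor therefore varies only between homes.

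Protocol article, Quantitative analyses: new ulcers are modelled from assessment to assessment by repeated-measures logistic regression fitted with GEE. On variance: "Robust standard errors, clustered at the facility level, will be employed to account for covariance among residents within facilities over time". A mixed model is offered to test robustness, "instead of GEEs using PROC GENMOD", with this reason: "With PROC GLIMMIX, we can use random effects to model the covariance rather than clustered standard errors". Facility staffing measures are among the listed predictors. Neither model is given a finite-cluster correction, a t reference or a degrees-of-freedom method.

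Protocol article, Statistical power: Aim 1 is described as a logistic regression across the three arms controlling for risk level, and GEE is named for Aim 2. The Aim 1 sample size is computed "with a power of 0.95 at a one-tailed significance level of α = 0.05, according to G*Power". Whether arms differ is then judged by overlap of 95% confidence intervals, and overlap counts as confirmation of no difference. A two-sided 5% level is also set, among the general methods in Quantitative analyses.

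**The concern.** The sandwich variance is justified when the number of independent clusters is large. Here a pairwise contrast has six clusters. With so few, the sandwich is biased downward and is itself highly variable, so a normal critical value is too small. More residents or more assessments per home do not help, because a facility-clustered sandwich still has only three independent contributions per arm.

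At stake is the comparison of 2-, 3- and 4-hour intervals. The trial could report an excess of ulcers with a longer interval about two and a half times as often as its one-sided 5% level states. It could also publish intervals for the arm contrast that miss the true value about one time in five.

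**Working it through.** **Inputs from the protocol.** Nine homes, three per arm; N = 951, 317 per arm, so 951/9 ≈ 106 per home; reference incidence 9.2% with SD 3.3% across homes; expected rate 3.5%; odds ratio 0.38; one-tailed 0.05; power 0.95.

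**Assumed input.** No ICC is given. The stated SD suggests a range:
- Net of binomial noise: 0.033² − 0.092×0.908/106 = 0.001089 − 0.000788 = 0.000301. Divided by 0.092×0.908 = 0.0835, this is 0.0036.
- If all the spread were between homes: 0.001089/0.0835 = 0.013.
- The checks run from 0 to 0.05.

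**The plan's own figure.** A logistic sample-size formula with a binary predictor, base rate 9.2%, odds ratio 0.38, one-tailed 0.05 and power 0.95 gives a total of 963 (Hsieh, predictor share 1/3) or 924 (Demidenko, share 1/2). Both are within 3% of 951. The figure thus reproduces as the total for one two-group contrast with no clustering term. The simple two-proportion formula needs 394 per arm, and 317 per arm gives about 90% power before any clustering.

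**Size of the distortion, analytically.** Take three equal homes per arm, with home proportions p_j and arm mean p̄.
- Sandwich variance of the arm mean: Σ(p_j − p̄)²/9.
- Unbiased variance: Σ(p_j − p̄)²/6.
- SE ratio: √(6/9) = √(2/3) = 0.816, about 18% too small.
- The correctly scaled statistic for a 3 v 3 contrast is roughly t with 4 df.
- One-sided 5%: 1.645 × 0.816 = 1.343, and P(t₄ > 1.343) = 12.5%.
- Two-sided 5%: 1.960 × 0.816 = 1.600, and P(|t₄| > 1.600) = 18.5%, so coverage is 81.5%.
- Interval half-width relative to the corrected one: 1.960 × 0.816/2.776 = 0.58.
- With an unbiased SE but still a normal reference, error would be 8.8% one-sided and 12.2% two-sided. In width, z for t costs a factor 1.960/2.776 = 0.71, more than the 0.82 from SE bias.

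**Simulation.** Beta-binomial, 100,000 trials per setting, incidence 9.2%, no true difference, uncorrected sandwich with a normal reference:

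| Homes | ICC | One-sided | Two-sided | Coverage |
|---|---|---|---|---|
| Equal size | 0 | 12.3% | 18.2% | 81.8% |
| Equal size | 0.0036 | 12.4% | 18.4% | 81.6% |
| Equal size | 0.01 | 12.7% | 18.4% | 81.6% |
| Equal size | 0.05 | 13.7% | 20.3% | 79.7% |
| Size CV 0.4 | 0 to 0.05 | 13.1–14.8% | 19.4–22.5% | 77.5–80.6% |

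At 3.5% incidence with equal homes the ranges are 12.1 to 15.2% and 17.7 to 22.3%. In logistic fits at ICC 0.01, adding risk level leaves error at 12.1 to 13.2% and 17.5 to 19.4%. Adding one facility-level covariate raises it to 14.5 to 15.1% and 22.9 to 23.7%.

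**Do the remedies work?** For three equal homes per arm, Kauermann-Carroll multiplies the variance by 1/(1 − 1/3) = 1.5 and Mancl-DeRouen by 1/(1 − 1/3)² = 2.25. At 9.2% incidence:
- Home-level t-test pooling all nine homes (9 − 3 = 6 df): about 5%.
- Kauermann-Carroll, 4 df: about 5%.
- Mancl-DeRouen, 6 df: about 4%.
- Kauermann-Carroll, 6 df: about 6 to 7% one-sided and 7 to 8% two-sided, so not restored.

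With home sizes varying (CV 0.4), Kauermann-Carroll with 4 df gives 5.2 to 6.4% one-sided across both incidences.

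**Cost in power.** For true rates of 9.2% v 3.5% at ICC 0.0036, one-sided power is about 57% (Mancl-DeRouen, 6 df), 65% (Kauermann-Carroll, 4 df) and 69% (home-level t on 6 df, third arm also at 9.2%). Under the overlap rule with arm-level intervals, moving from the plain sandwich to Kauermann-Carroll with 4 df cuts non-overlap from about 66% to 27%. At ICC 0.013 it falls from 49% to 16%.

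**The case against.** **Silence is not refusal.** The article neither adopts nor rejects a small-sample correction, and an unseen analysis plan may add one. That stands as a condition: the error rates are those of the method as written. But the protocol does fix the estimator, the clustering level and the procedure, and a plain facility-clustered sandwich suits nine homes badly.

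**Scope.** A reader might infer that every arm comparison and every interval in the trial is affected. The text does not support that. Statistical power describes Aim 1 as a logistic regression and names GEE for Aim 2, so whether the robust-variance sentence governs Aim 1 is unclear. The mixed model is a second clustered analysis, though only a robustness check and with no degrees-of-freedom method.

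**Size.** It is tempting to call the standard errors far too small and to quote one error range of 12 to 20%. The SE bias alone is about 18%, and the larger part of the lost width comes from z in place of t. The range would also join two different tests: the arm test is one-tailed, so 12 to 14% is the figure that applies to it.

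**Decision rule.** If arm-level 95% intervals are compared for overlap, false separation at 9.2% incidence is about 10% with equal homes and up to about 13% with unequal ones, not 20%. Too-narrow intervals also overlap less, so the defect works against the conclusion of no difference that the investigators expect. This stands. It does not rescue the one-tailed tests, to which the plan also commits, or the coverage of the contrast interval.

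**Conclusion.** The concern holds for the arm contrast from the GEE as written. At 9.2% incidence and equal home sizes, a one-sided 5% test errs about 12 to 14% of the time, a two-sided 5% test 18 to 20%, and a 95% interval for the contrast covers about 80 to 82%. Unequal home sizes or a facility-level covariate make this somewhat worse.

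The result rests on three homes per arm, which the protocol fixes, and on no correction being applied, which is read from the text. It hardly depends on the ICC and is present at zero. The power figures do depend on the ICC. They use 0.0036, which treats the quoted 9.2% and SD of 3.3% as applying to homes of about 106 residents over the study period.

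**What to change.** 1. State which model governs the arm comparison in Aim 1, and that the same inference method applies to Aims 1 and 2.
2. Make one of these primary for arm comparisons: a home-level analysis of risk-adjusted incidence with a t reference on 6 df; GEE with a Kauermann-Carroll sandwich and 4 df; or GEE with a Mancl-DeRouen sandwich and 6 df, which is slightly conservative. Do not pair Kauermann-Carroll with 6 df. The 6 df of the home-level analysis assume no facility-level covariate in the primary contrast.
3. Keep the uncorrected GEE as descriptive only.
4. Report the confidence interval for the arm contrast itself, and stop treating overlap as confirmation of no difference. Without this step the correction alone would make a true difference of the planned size more likely to be read as none.
5. Restate the power. The planned 95% does not hold under any of these methods: about 57 to 69% at ICC 0.0036 for 9.2% v 3.5%.

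Cost: no new data and a short change to the model specification. PROC GLIMMIX, already named, offers bias-corrected sandwich estimators and degrees-of-freedom options. The real price is wider intervals and an openly lower power.

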##### Statistical power.

According to previous research, the average PrU incidence rates range from 5.2–15%. At the time of study design, the nine NHs within the NHS were identified with the highest PrU incidence rates which averaged 9.2% (SD = 3.3%). In power analyses, we used 3.5% for PrU incidence as the expected rate for intervention since it is the highest rate found in the TURN study (for moderate-risk patients). The PrU incidence rates have been translated into an odds ratio of 0.38 (= 3.5%/9.2%) as the effect size to detect. For Aim 1, odds ratios from a logistic regression of PrU incidence rates in the three treatment arms (i.e., at 2-, 3-, and 4-h repositioning frequencies), controlling for risk level, are proposed to test the difference in PrU incidence rates between the 4-h arm and the 2-h arm as well as between the 4-h arm and the 3-h arm at 4 weeks; we are assuming that the distance between the 2-h arm and the TURN 3-h odds ratio will be larger. A sample size of *N* = 951 (*n* = 317 for each arm) will be required to detect an odds ratio of .38 with a power of 0.95 at a one-tailed significance level of α = 0.05, according to G*Power. We are using a power of 0.95 instead of the conventional power of 0.80 to ensure that we will have a smaller Type II error to test the hypothesis of no-group difference that we expect to fail to reject. We are using a one-tailed test since we are only interested in determining whether the PrU rate is higher for assigned repositioning intervals longer than the current 2-h standard practice.. For Aim 2, GEE is proposed. A sample size of *n* = 114 for each group (total *N* = 342) will be required to detect an effect size of 5.7% (= 9.2% - 3.5%) with a power of 0.80 at a one-tailed significance level of α = 0.05, using the algorithms GEESIZE developed by Dahmen, et al., on an autoregressive structure for residual correlations [48]. Since the nine NHs will be randomly assigned to the three treatment arms, risk level will be the only potential covariate to be controlled in the models, and this is already considered in the power analyses. Therefore, we will target a sample size of *N* = 951 (the larger of the two required sample sizes) for both aims while taking into account potential losses due to turnover, attrition, and exclusion criteria. While this proposed study may look like a non-inferiority or equivalence trial, we will run regular one-tailed superiority tests, because (as noted earlier) we are only interested in examining whether or not the PrU rate is higher for less frequent repositioning than for the standard 2-h repositioning. (We assume that 2-h repositioning was followed to produce the 9.2% average PrU incidence rate across our 9 study NHs, because that is the current standard of care). Also, according to Snapinn [49], non-inferiority trials have many controversial assumptions and limitations that need to be made or addressed, and that is beyond the control of our study. For incidence, it is difficult to specify a non-inferiority margin for PrU rates. Instead, we will test the hypothesis of no group-difference by examining whether the 95% confidence intervals of the odds ratios (for Aim 1) or the PrU rates (for Aim 2) of the two pairs of compared groups (e.g., 4-h arm vs. 2-h arm and 4-h arm vs. 3-h arm) overlap. If the confidence intervals do overlap, the hypothesis for no-group difference will be confirmed.

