#### Analysis

##### Quantitative analyses.

We hypothesize that there will be no significant difference in PrU incidence between the 3 treatment arms in the study using three risk level groups: high risk (Braden Scale Score, 10–12), moderate risk (Braden Scale Score, 13–14), and low risk (Braden Scores > 14). The hypothesis of no group difference will be tested by examining whether the 95% confidence intervals of the rates of PrU and the 2-h repositioning overlap. If so, the hypothesis for no group difference will be confirmed. We will also determine how changes in medical severity components (as measured by a modified Comprehensive Severity Index), change in clinically assessed risk level (low, moderate, high as measured by the Braden Scale) and their interactions with repositioning schedule are associated with PrU development.

Descriptive statistics will be used to examine resident status, interventions, outcomes, and cost elements. For categorical variables, we will create contingency tables and use chi-squared or Fisher’s exact tests to determine the significance of bivariate differences. For continuous variables, we will use analysis of variance or non-parametric tests, depending on variable distributions. A two-sided *p*-value < 0.05 will be statistically significant. Intervention cost by NH and study arm and incremental cost-effectiveness ratios (ICERs) will be calculated and compared for cost per percentage reduction in PrUs. Sensitivity analysis will be conducted with the range of observed repositioning times, nurse salaries, and market prices for non-labor inputs to assess the robustness of the ICERs and their sensitivity to labor and non-labor input prices.

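### With 317 residents per arm, the Aim 1 pairwise comparisons have power of about 0.9 before clustering, not 0.95, and the stated odds ratio of 0.38 is a risk ratio

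*Protocol article*

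**What the plan says.** All the sizing for Aim 1 is in the Statistical power section of the protocol article.

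- **Reference rate.** "We assume that 2-h repositioning was followed to produce the 9.2% average PrU incidence rate across our 9 study NHs".
- **Expected rate.** "we used 3.5% for PrU incidence as the expected rate for intervention".
- **Effect size.** "The PrU incidence rates have been translated into an odds ratio of 0.38 (= 3.5%/9.2%) as the effect size to detect".
- **Comparisons.** The logistic regression is to test the difference "between the 4-h arm and the 2-h arm as well as between the 4-h arm and the 3-h arm at 4 weeks".
- **Sample size and power.** "A sample size of *N* = 951 (*n* = 317 for each arm) will be required", "with a power of 0.95 at a one-tailed significance level of α = 0.05, according to G*Power".

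The section explains that 0.95 was preferred to the usual 0.80 because the investigators expect not to reject the null hypothesis and want a small Type II error. It states no intracluster correlation and no design effect. The Resident sample section gives 951 as the number for analysis and 1100 as the enrolment aim.

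**The concern.** Two things do not fit together. First, the effect size is formed by dividing two risks but is called an odds ratio, and is then carried into a logistic-regression calculation, where the two are not interchangeable. Second, the power is claimed for comparisons between two arms, yet 951 is the total over three. Any one comparison has 634 residents.

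The plan intends to conclude that the intervals do not differ, so a missed difference is the error that would mislead. The claim of a 5% Type II error is what the plan offers as protection. If 317 per arm does not deliver it even with independent residents, a reader will place more confidence in a null result than the design supports.

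**Working it through.** **Inputs**, all from the Statistical power section: p1 = 0.092, p2 = 0.035, n = 317 per arm, one-sided α = 0.05 (z = 1.645), target power 0.95 (z = 1.645). Residents are taken as independent, which is the most favourable case.

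**1. Effect size**

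- Risk ratio: 0.035/0.092 = 0.380. This is the plan's figure.
- Odds ratio: (0.035/0.965)/(0.092/0.908) = 0.03627/0.10132 = 0.358.
- Conversely, an odds ratio of 0.38 from 9.2% gives odds of 0.38 × 0.10132 = 0.03850, so a rate of 0.03850/1.03850 = 3.71%, not 3.5%.

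**2. Pairwise power at 317 per arm**

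Two-proportion test with pooled null variance, where p̄ is the mean of p1 and p2:

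power = Φ{ [ |p1 − p2| − 1.645·√(2p̄(1−p̄)/n) ] / √[(p1(1−p1) + p2(1−p2))/n] }

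- 9.2% vs 3.5%: p̄ = 0.0635; Φ[(0.0570 − 1.645 × 0.01937)/0.01924] = 0.904.
- 9.2% vs 3.71%: Φ[(0.05493 − 1.645 × 0.01952)/0.01939] = 0.880.

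Wald test of the log odds ratio, with SE² = 1/[n·p1(1−p1)] + 1/[n·p2(1−p2)]:

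- 9.2% vs 3.5%: Φ(1.0273/0.3622 − 1.645) = 0.883.
- Odds ratio 0.38: Φ(0.9676/0.3551 − 1.645) = 0.860.

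Other methods, same inputs:

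| Method | 9.2% vs 3.5% | Odds ratio 0.38 |
|---|---|---|
| Two-proportion z, formula | 0.904 | 0.880 |
| Logistic Wald | 0.883 | 0.860 |
| Logistic, variance-corrected | 0.913 | 0.890 |
| Exact enumeration, pooled z | 0.915 | 0.891 |
| Exact enumeration, Fisher | 0.886 | 0.858 |

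None reaches 0.95. Type II error runs from 1 − 0.915 = 0.085 to 1 − 0.858 = 0.142, which is 1.7 to 2.8 times 0.05.

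**3. Size needed for 0.95**

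- Two-proportion formula: 394 per arm (3 × 394 = 1182 in all) for 9.2% vs 3.5%; 431 per arm (1293) for odds ratio 0.38.
- Wald: 427 and 463 per arm respectively.
- Across the logistic formulas for odds ratio 0.38 and a 50:50 split, the two arms together need 843 to 924 residents, or 422 to 462 per arm.

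**4. Where 951 may come from**

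The section does not give the full G*Power settings, so this is inference. The number does arise as a total N for a single two-level predictor. With base rate 3.5%, odds ratio 2.63 (= 1/0.38) and one third of residents exposed, the Wald formula gives 951. With base rate 9.2%, odds ratio 0.38 and a share of 0.67, the variance-corrected formula gives 952. That describes one arm against the other two pooled, or more generally a single two-group total later divided by three. It is not the pairwise contrast that the section names.

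**5. Two-sided testing**

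The Quantitative analyses section says: "A two-sided *p*-value < 0.05 will be statistically significant". If that applied to the arm comparisons, the formulas in step 2 would give 0.81 to 0.84 for 9.2% vs 3.5% (two-proportion 0.839, Wald 0.810) and 0.78 to 0.81 for odds ratio 0.38 (0.805 and 0.778).

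**The case against.** **The mislabel is conservative.** An odds ratio of 0.38 is a smaller effect than 0.358, so correcting the label alone raises power from 0.880 to 0.904. This is right, and the label on its own does no harm to the sizing. Power still stays below 0.95.

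**Enrolment is to be 1100, and residents who leave stay in the analysis.** If all 1100 were analysed, about 367 per arm, power for 9.2% vs 3.5% would be 0.92 (Wald) to 0.94 (two-proportion). That narrows the gap without closing it, and 951 is the stated number for analysis.

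**The third arm or covariate adjustment might make up the difference.** Neither does. With arm as a three-level factor, the third arm adds essentially nothing to a contrast between the other two. An allowance for correlation with risk level would raise the required N.

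**The two-sided figure is weakly grounded.** The two-sided sentence stands in a paragraph on descriptive and bivariate tests, while the power section argues for one-tailed tests. That is fair. The conclusion here rests on the one-sided figures only.

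**A power of 0.9 is still good, and other features matter more.** Clustering and the decision rule based on overlapping confidence intervals may indeed matter more, and 0.9 is not the power of that overlap rule. These are separate matters. They do not make the 0.95 correct.

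**Conclusion.** The concern holds on both counts. The effect size is a risk ratio of 0.38, equivalent to an odds ratio of 0.358. At 317 per arm, pairwise one-sided power is about 0.88 to 0.92 for the plan's own rates and 0.86 to 0.89 for an odds ratio of 0.38, against a stated 0.95. This rests only on the plan's rates, arm size and α, and on independent residents. It does not depend on how 951 was obtained.

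The shortfall is moderate before clustering and would grow with any positive intracluster correlation. The article gives none. By way of illustration, with 317/3, or about 106, residents per home and design effect 1 + (317/3 − 1)·ICC, assumed ICCs of 0.005, 0.01, 0.02 and 0.05 give power of about 0.77, 0.66, 0.51 and 0.32 for 9.2% vs 3.5%. That is before any allowance for having only three homes per arm.

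**What to change.** In the Statistical power section:

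1. Replace the effect-size label with a risk ratio of 0.38 (odds ratio 0.36).
2. State that 951 covers three arms and that each Aim 1 comparison uses 634 residents.
3. Restate pairwise power at 317 per arm as about 0.9 for 9.2% vs 3.5% at one-sided 0.05 before clustering, or 0.86 to 0.89 if an odds ratio of 0.38 is kept as the target. Name the formula and the software settings.
4. Add the cluster-adjusted power, with the assumed ICC, its range and its source.
5. Amend the sentence that justifies 0.95 by its small Type II error, since that error is about 0.085 to 0.14 before clustering.

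The cost is corrected figures in one section and a less favourable stated power. Enrolment and conduct do not change.
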